**Intervention**			
	Introduction to managers		1
	Training educators (workshop)		1
	Introduction to parents		1
	Baseline data collection		1
	LEAP activity units every day		1-6
	Providing ongoing support for educators		1-6
	Booster session for educators at month 3		1-6
	Resources and monthly sessions for parents		1-6
	Filling daily logs, weekly reports and comments (increasing intervention efficacy)		1-6
	Postintervention data collection		6
	Feedback from staff and parents		6
**Control**			
	Baseline data collection		1
	Conventional programs in preschools		1-6
	Final data collection		6

**Table 4 table4:** A list of variables, tools, and data collection points.

Variable	Assessment tool	Timing
Sociodemographic data	Questionnaire	Baseline
Anthropometry (children)	Weight, height, waist and arm circumference, body mass index percentile, and body mass index *z*-scores for age	Baseline/End
Nutrition risk (children)	Nutrition Screening Tool for Every Preschooler	Baseline/End
Food intake and eating habits	24-hour recall×3	Baseline/End
Physical activity level (children)	Children attitude toward physical activity Physical activity level at home Physical activity level by pedometers
Quality of life (children)	Pediatric Quality of Life Inventory questionnaire	Baseline/End
Efficiency and adequacy of the parent material	Interview with parents	End
Feasibility of the program (weaknesses and strengths)	Interview with managers and educators	End

#### Variables of Interest

Several variables are considered to assess the defined objectives, which are specified earlier. Table 4 presents the main outcome measures that are administered among both intervention and control participants.

##### Sociodemographic Information

This questionnaire provides demographic data, such as parents’ status, age, education level, job, family income, as well as some known childhood obesity associated variables such as parent-reported weight and height, duration of child exclusive and nonexclusive breastfeeding, age of solid food introduction, age of starting kindergarten, eating in front of screen, physical and sedentary behaviors, and some general parenting habits such as child force-feeding, use of food as reward or punishment, parents role model or the presence at meal time, and parental controlling approach.

##### Nutritional Assessment

###### Diet Quality

Children’s food intake is assessed by the 24-hour recall for each child, which is filled for 3 days (2 regular days and 1 holiday) with a 14-day interval, at baseline and after the intervention. As parents provide children’s midday snack themselves and educators are obligated to provide daily reports for parents about the amount of snack their child has eaten, parents are the best source for receiving the data of children’s food intake. The Youth Healthy Eating Index (YHEI) was used for the analysis of the diet quality out of food recalls [31,32]. The YHEI focuses on the total fat, sodium, and saturated fat in children’s diet by examining food choices rather than a direct calculation of the nutrient intake. Furthermore, the YHEI focuses on trans-fatty acids, added sugar, and low fiber in children’s diet, unlike the conventional Healthy Eating Index [31].

###### Nutrition Risk

The NutriSTEP [33,34] has been first designed and validated in Canada in different languages for assessing eating habits and nutrition problems in children aged 3-5 years. A license was obtained from the developers of NutriSTEP questionnaires. The Persian version of NutriSTEP was used after translation and cross-cultural adaptation [35]. The NutriSTEP scoring system categorizes children into low, medium, and high risk in terms of nutritional status. It covers 4 main domains related to children’s food intake as follows: (1) food and fruit intake; (2) physical growth and development; (3) factors affecting the food intake and eating behavior; (4) physical activity and sedentary behavior.

###### Anthropometry

Weight, height, midarm circumference, and waist circumference are obtained from all participants, at baseline and after completion of the intervention, according to the standardized protocol [36]. Weight is measured using the Beurer BG13 Digital Scale, Germany, with a measuring rod of 0.1 kg and height using SECA 206 stadiometer, Germany, with a measuring rod of 0.1 cm. The waist and arm circumference are measured to the nearest 0.1 cm. Body mass index (BMI), BMI percentile, and BMI *z*-score are calculated using AnthroPlus software, version 1.0.4, Geneva, WHO, 2009 [37].

##### Physical Activity Assessment

The physical activity level is assessed using subjective and objective instruments.

###### Children Attitude Toward Physical Activity

This index is assessed through a 25-item, Likert scale validated questionnaire, which is answered by children with the assistance of an interviewer (educators) and scores children’s attitude and degree of attraction toward physical activity [38,39]. The Children Attraction toward Physical Activity (CAPA) original questionnaire was translated into Persian and culturally adapted, based on the current guidelines for translation and cross-cultural adaptation of questionnaires [35]. The Persian version of the CAPA questionnaire has excellent internal consistency among Iranian preschool children after omitting 4 questions (Cronbach alpha=.93).

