#### The Intervention

The IHS program has 6 components (Table 1):

*Customized LEAP*: Comprises two illustrated handbooks.Physical activity: containing 20 activity units along with a complementary chapter containing information for educators (ISBN: 2-25-7457-600-978).Nutrition: containing 20 activity units along with a complementary chapter containing information for educators (ISBN: 9-26-7457-600-978).The activity units were translated and customized on the basis of the criteria discussed during the “customization” process. This handbook is accompanied with “Healthy-kid Toolkit,” which contains utilities and materials for LEAP activity units.*IHS Implementation Guide*: A handbook for managers and educators containing modified self-assessment tool, as well as principles of the program, action planning, policies and practices, details of implementation, log pages, and report pages for both educators and managers. It also contains a suggested healthy weekly menu for serving a snack or a hot meal for children at preschool.*Training and Monitoring*: Comprises on-site training workshop followed by a supplementary booster session during the implementation (3-4 hours), as well as ongoing support through mobile and internet-based contacts (telegram) and weekly visits. The initial workshop introduces the program, objectives, customized LEAP activity units, IHS Toolkit, and resources. Educators and managers of intervention centers are invited to become a member of the IHS telegram channel, which is the most popular internet-based social network among Iranians. The implementation is monitored by weekly visits and daily logs and checking videos and photos while children do the activities every day.*Building Partnership*: Attracting the participation of key stakeholders and policy makers:Ministry of Health and Medical Education: Nutrition Affairs Department of the Ministry was informed about the details of the project from the inception of the project. The results of this pilot study will be reported to the aforementioned department for further steps toward the national implementation of the program.Provincial broadcasting (radio and television): A television show and radio talks related to childhood obesity, physical activity in children, healthy nutrition, parenting, and many other related topics were recorded to introduce the program and report the future outcomes.Provincial Education Department: Aiming at incorporating this program or any of its components into the current preschool education bylaws, several meetings were arranged with heads-in-charge.*Parent Engagement*: This is the main distinction between HSDS and IHS and includes the following:A scientific, user-friendly, and simple book entitled, “Knowledgeable Parents, Healthier Children,” for parents aiming at improving their knowledge and practice regarding healthy eating for the whole family, especially their preschool child (ISBN: 5-24-7457-600-978).Routine monthly meetings between parents and IHS team nutritionists.A 107-page book, which is written for parents, contains 5 main chapters as follows: (1) childhood obesity, the epidemic health problem; (2) the importance of healthy nutrition and physical activity for children; (3) the role of parents in children weight management; (4) parental challenges and worriment; and (5) specific nutrition and activity considerations for a preschool child. Parents are asked to read each chapter during one month. In monthly meetings, the content of each chapter is again explained and discussed for parents. These parent-nutritionist meetings are mutual, and parents are allowed to ask questions or share their comments or experiences regarding children’s nutrition and activity issues. This book is written by 2 team members ([name]). Before releasing this resource, 3 collaborating mothers were selected to read the book and share their comments regarding the fluency, practicality, and usefulness of content, as well as suggestions for adding topics or other required data.*Communication and Knowledge Exchange*: The purpose of this component is maintained by a comprehensive website [30] containing details of the program, pages for managers, educators, parents, and children, as well as social media tools and reports of the study findings for the stakeholders. This component is expected to improve knowledge, engagement, motivation, and level of cooperation in stakeholders, as well as knowledge translation and dissemination of the program and findings.

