#### Development of the Evaluation Plan

##### Study Design

The evaluation of the IHS program is designed as a pilot randomized controlled trial. For recruitment, officially registered preschools in the Provincial Education Department database are stratified according to the socioeconomic status of people living in that area. The three levels of high, middle, and low socioeconomic areas are defined according to the categorization of the Provincial Education Department. Two preschools are randomly selected from each socioeconomic level (a total of 6 centers) and then allocated to the intervention and control groups (Figure 1). Overall, 3 centers in the intervention group (each center belongs to a different socioeconomic level) and 3 centers in the control group are defined. The selected centers are contacted in person and provided with comprehensive information. After confirmation of managers, 2 classes are randomly selected for enrollment (6 classes in the intervention group and 6 classes in the control group). Then, the parents of eligible children are invited in a meeting in preschool, and informed consent is obtained after a brief introduction on the whole program and the role of parents (for parents of the intervention group) and informing parents for data collection and cooperation in filling questionnaires (for parents of the control group). The components of the intervention program for managers, educators, children, and parents are conducted in intervention classes, and control classes receive the conventional preschool education program. Aiming to acknowledge the cooperation of control preschools, the wait-list approach is suggested to the managers to receive the intervention in the next educational year, as well as a comprehensive report for growth, nutrition, and physical activity status of each child, which is given after the intervention, is completed.

The intervention lasts for 6 months. The duration of an educational year in preschools in Iran is the same as elementary schools and lasts for 8 months (October-May). From March 21, there are around 2-week New Year (Norouz) holidays. The intervention will be completed before Norouz holidays. The required data are collected at baseline and after the completion of the intervention period.

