##### Participants and Data Collection

In the Iranian preschool bylaws, preschool is not a mandatory level, and all children aged 4-6 years can be registered either in preschool-1 (age, 4-5 years) or preschool-2 (age, 5-6 years). All children aged 4-6 years of the selected classes of each center are included in the study after a valid consent from their parents or legal guardian, while those with known chronic disease, such as cardiovascular, respiratory, endocrine, or musculoskeletal problems—after physician inquiry—as well as those who need to adhere to a specific diet, such as gluten-free or phenylalanine-free diets, are excluded.

Data reflecting the nutrition status, diet quality, physical activity and sedentary behaviors, quality of life, and anthropometry of children, as well as the general sociodemographic status of participants and their families are collected at baseline and after the intervention is completed (Table 3). Data collection is performed by a team of 4 nutritionists who are given comprehensive training to standardize the data collection. They learned how to consistently obtain anthropometric measurements, fill the required questionnaires, and train the use of pedometers and filling the parent-report questionnaires to parents. Data entry is done by one person for consistency (a PhD student). Each preschool takes about 7-10 days to collect all the required data. As parents’ cooperation is very important in the data collection, aiming to acknowledge their cooperation, especially in control preschools, a gift for children and a free nutrition consultation for children and their parents, as well as a comprehensive report for child growth, nutrition, and activity status, are dedicated.

As this is a pilot study and we cannot estimate the attrition rate, there is no need to define the sample size, but sample characteristics represent the population of preschool children in Mashhad.

**Table 3 table3:** Overview of the study process.

Group and action		Months	

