### Implementation

#### Training Educators

Aiming at empowering educators and integration of the implementation among intervention centers, a workshop at baseline and a booster session at the middle of the intervention period is conducted. Details of LEAP activities, activity demonstrations, role of educators, collaboration with parents, and other related implementation hints are presented and discussed.

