#### Process Evaluation and Monitoring

The Reach, Effectiveness, Adoption, Implementation, and Maintenance framework is used to assess the implementation process [24]. Educators are asked to fill logs every day containing the code of activity unit, the time spent on each unit, and feedback of children learning. Photos or videos of LEAP activities are received by the implementation team every day through internet-based contacts (telegram channel). A team member has on-site weekly visits to ensure the standard implementation of the whole program and the activities.

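### The attraction-to-physical-activity interview is assigned to educators, which does not fit the stated nutritionist data-collection team and carries a risk of differential interviewer bias

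*Protocol article*

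**What the plan says.** The protocol article names two different groups for the same task.

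- **Participants and Data Collection** makes a general statement with no exception for any instrument: "Data collection is performed by a team of 4 nutritionists who are given comprehensive training to standardize the data collection". The training covers questionnaires as well as body measurements: "They learned how to consistently obtain anthropometric measurements, fill the required questionnaires".
- **Children Attitude Toward Physical Activity** says of the CAPA questionnaire, a 25-item Likert instrument, "which is answered by children with the assistance of an interviewer (educators").

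The educators' part in the intervention arm is described in three places.

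- **The Intervention**, on training: "The initial workshop introduces the program, objectives, customized LEAP activity units, IHS Toolkit, and resources".
- **Training Educators**, on the workshop and booster: "Details of LEAP activities, activity demonstrations, role of educators, collaboration with parents, and other related implementation hints are presented and discussed".
- **Process Evaluation and Monitoring**: "Educators are asked to fill logs every day containing the code of activity unit, the time spent on each unit, and feedback of children learning". The same section adds daily photos or videos and weekly on-site visits.

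Under **Study Design**, "control classes receive the conventional preschool education program". The study objectives (Textbox 1) list an increase in attraction to physical activity among the effects the program is meant to show.

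**The concern.** CAPA asks very young children to rate how much they like physical activity, with an adult helping them answer. Such answers can be moved by how items are explained, by prompting, and by the child's wish to please the adult. If the adult's position were the same in both arms, this would mostly add noise. Here it differs by arm: in the intervention centers the helper has been taught the aims of the program, works with it every day and is monitored on its delivery.

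A between-arm difference in CAPA could then reflect the program, the interviewer, or both. More children would not help, because a systematic shift does not shrink with sample size. What is at stake is the conclusion on one named objective. Pedometer steps, anthropometry and the parent-reported measures are not touched by this point.

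**Working it through.** The document gives no figure for interviewer effects, so there is nothing to reproduce. The check sets the statements side by side and then asks whether the planned analysis could absorb the problem.

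**1. Do the two statements fit together?** The general section gives data collection to four nutritionists and presents their training as the means of standardization. The CAPA section gives the interviewer role to educators. The article describes program training for educators but no data-collection training. As written, the claimed standardization does not cover CAPA.

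**2. Does the interviewer differ by arm?**

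| | Intervention educators | Control educators |
|---|---|---|
| Told the program objectives | Yes, initial workshop | Not described |
| Activity units | Every day, months 1-6 (Table 3) | Conventional program |
| Daily logs, including children's learning | Yes | Not described |
| Monitored on delivery | Weekly visits, daily photos or videos | Not described |

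The asymmetry follows from the design, not from an omission in the article.

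**3. Would the baseline measurement remove it?** Let *d* be the true effect on CAPA, and let *b0* and *b1* be the interviewer shift (intervention minus control) at baseline and at the end.

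- Comparison of end values: expected difference = *d* + *b1*.
- Comparison of changes: expected difference = *d* + (*b1* − *b0*).
- Analysis of covariance with baseline slope *k*: expected difference = *d* + *b1* − *k* × *b0*.

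The change comparison is free of interviewer bias only if *b1* = *b0*. Table 3 lists the educator workshop before baseline data collection, both in month 1, so some shift may already be present at baseline and would partly cancel. Six months of delivery, logging, a booster session and monitoring then lie between the two waves, so *b1* may exceed *b0*. Baseline adjustment may reduce the problem but cannot be relied on to remove it.

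**4. Does the reported reliability help?** The Cronbach alpha of .93 shows that items agree with one another. A prompt that moves all items the same way leaves that agreement intact, so it says nothing on this point.

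**5. Cost of using the named team.** Children: 152 + 148 = 300 (Data Analysis). Nutritionists: 4. Minutes per child are not given and are assumed.

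- 5 minutes: 300 × 5 / 60 / 4 = 6.25 hours per nutritionist per wave.
- 10 minutes: 300 × 10 / 60 / 4 = 12.5 hours.
- 15 minutes: 300 × 15 / 60 / 4 = 18.75 hours.

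At 10 minutes, spread over 6 centers, this is 12.5 / 6 = about 2.1 hours per nutritionist per center, against the 7-10 days the article allows for data collection at each preschool.

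**The case against.** The best defense is that a general sentence and a specific one need not conflict. The data-collection section itself shows that the team does not administer everything directly, since it trains parents to complete the parent-report forms. Educators might likewise have helped with one instrument under the team's direction. That reading is possible, but the article does not state it, and it would not change who sits with the child. The wording still needs to be reconciled.

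A second defense is that control centers are not naive: all selected centers were given comprehensive information, and control managers were offered the program for the following year. This narrows the contrast in awareness. It does not make control educators trained deliverers.

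A third is that the measure is repeated, so a constant shift cancels. This stands in part, as shown in the working.

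A fourth is that this is one subjective measure among many in a pilot. That is right, and it limits the weight of the point to CAPA.

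Some stronger readings are tempting, but the document does not support them:

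- **That each child was interviewed by his or her own class educator.** The CAPA section says only educators. The article uses that word for preschool staff, but does not tie the interviewer to the child's class.
- **That outcome measurement generally is compromised because nutritionists also lead the parent meetings.** The article lists "Routine monthly meetings between parents and IHS team nutritionists" as part of the intervention, but does not say that these are the four data collectors. Separation of staff roles is also a detail an article may leave to the full protocol.

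**Conclusion.** The point holds as an unreconciled statement of who conducts CAPA, together with a risk of differential interviewer bias toward the intervention on one named objective. It rests on two things the document states: educators assist with the interview, and intervention educators are trained in and implement the program while control educators are not. The direction is a reasonable inference. It assumes that adults who know and deliver a program may, without intending to, encourage favorable answers from children aged 4 to 6.

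The size cannot be derived from the document. A reader might infer that bias has been shown, or might put an assumed shift through the two-sample test and quote the resulting false-positive rate. Neither is supported. The article contains no data on interviewer effects, and such a rate would only restate the assumed shift while treating children from 6 centers as independent. The point is a worthwhile, low-cost improvement, not a flaw that undermines the trial.

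**What to change.** Reconcile the section on participants and data collection with the CAPA section, so that both name the same interviewers. Have the existing team of four nutritionists conduct the CAPA interview in both arms at both time points, without educator assistance. No additional staff category is needed. The downside is added interview time for that team: about 12.5 hours each per wave at an assumed 10 minutes per child (6.25 to 18.75 hours for 5 to 15 minutes).

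The article reports that the intervention was completed by the end of March 2018 and that analysis was under way. For this trial the usable part therefore lies in reporting, and the change of interviewer applies to any later wave or wider roll-out. Where educators have already done the interviews:

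- state who interviewed in each arm and at each wave;
- report CAPA as unblinded and exploratory;
- draw no efficacy conclusion on attraction to physical activity from CAPA alone.

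Pedometer steps can inform the conclusion on activity level, but they do not measure attraction and cannot stand in for CAPA. The reporting changes cost a few sentences.
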